## Abstract

This manuscript describes the rationale and design of a family-based, Hispanic sexual minority youth (HSMY) specific preventive intervention, *Familias con Orgullo* (Families with Pride). HSMY (*N* = 306) and their primary caregivers will be recruited in South Florida and be randomized to Familias con Orgullo or prevention as usual. The intervention will be delivered by trained study facilitators. Outcomes will be measured at baseline and 6-, 18-, and 30-months post-baseline. The goals of this study are to evaluate whether the Familias con Orgullo intervention, compared to community practice, is effective in reducing drug use and depressive symptoms through the improvement of parent support for the youth, parent acceptance, family functioning, youth stress, and sexual minority stress. Additionally, we will explore whether gender and baseline levels of parent support for the youth, parent acceptance, family functioning, youth stress, and sexual minority stress moderate intervention effects on the youth outcomes.

**ClinicalTrials.gov identifier:**
NCT06057337, First posted September 28, 2023.

## Introduction

Hispanic sexual minority youth (HSMY) face a disproportionate burden of drug use and depressive symptoms [1–3] relative to both Hispanic non-sexual minority peers [4, 5] and non-Hispanic White sexual minority youth [6]. Despite the pervasive health disparities for HSMY, there are limited evidence-based interventions available for the prevention/reduction of drug use and depressive symptoms [7, 8]. Moreover, the limited interventions that are available do not include the family and are not culturally-syntonic, meaning that they do not address Hispanic cultural values and beliefs [7, 8]. Including these two components is particularly important for HSMY because in many cases, Hispanic families may be less accepting of their youth’s sexual orientation due to cultural values and beliefs [9] thereby increasing risks for drug use and worsening health related outcomes for HSMY [10, 11].

Given the centrality of family for HSMY and the possible impact family may have on health outcomes, studying risk processes only at an individual-level may not capture other simultaneously operating risk processes (e.g., parent support for the adolescent, parent acceptance, family functioning). Important family level factors suggest that there is a need for family-based interventions to address the health disparities HSMY face as it relates to drug use and depressive symptoms. Extensive research has documented the efficacy and effectiveness of family-based interventions for the prevention and/or reduction of drug use and depressive symptoms [12, 13], however, these interventions were not originally developed for HSMY and do not address the unique needs of this population [14]. Despite the evidence that family-based interventions can improve health outcomes for Hispanic youth and the importance of highlighting and supporting family influences on sexual minority health [15, 16], there is a dearth of evidence-based, culturally congruent family interventions that target the multiple risk and protective factors relevant to HSMY and their families to ameliorate health disparities related to drug use and depressive symptoms. Therefore, the purpose of this manuscript is to describe the protocol for a randomized controlled trial to evaluate the efficacy of Familias con Orgullo.

To evaluate the efficacy of Familias con Orgullo in preventing drug use and depressive symptoms, this study will use a randomized trial design with two arms (Familias con Orgullo and community practice; see study design and intervention conditions below). We hypothesize that Familias con Orgullo will be efficacious, compared to community practice, in decreasing past 90-day drug use frequency and quantity and depressive symptoms among HSMY, over 30-months and that the intervention effects on youth outcomes will be partially mediated by changes in parent support for the youth, parent acceptance, family functioning, youth stress, and sexual minority stress. In addition to our main hypothesis, this study also aims to explore whether gender and baseline levels of parent support for the youth, parent acceptance, family functioning, youth stress, and sexual minority stress moderate intervention effects on the youth outcomes. We hypothesize that gender and baseline levels of parent support for the youth, parent acceptance, family functioning, youth stress, and sexual minority stress will moderate intervention effects on youth outcomes such that youth at higher risk (e.g., families reporting higher stress, lower support, and poorer family functioning) will benefit most from Familias con Orgullo.

## Materials and methods

This study was approved on April 13, 2023, by the University of Miami Human Subjects Research Office, study # 20230372. The enrollment schedule, intervention, and assessments are available in Fig 1. During the time of manuscript preparation, participant recruitment had not yet begun. The authors confirm that all ongoing and related trials for this intervention are registered. Recruitment is scheduled to last 21 months from January 2024 and follow-up assessments will run through December 2027.

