### Study design

This study uses a randomized trial design with two arms (Familias con Orgullo and community practice) as the between subjects factor with four assessments at baseline and 6-, 18-, and 30-months post baseline as the within subject factor. Dyads of Hispanic youth (*N* = 306) and their primary caregivers (i.e., parents, which may include: mother, father, or legal guardian) will be randomly assigned to Familias con Orgullo or the community practice condition. Participants will be randomized on a 1:1 randomization ratio. An urn randomization will ensure comparability across conditions on the following variables (see measures section below): (1) current drug use (yes/no) and (2) level of depressive symptoms (below 16 on the CES-D or greater than or equal to 16).

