To recruit participants, trained assessors will approach families (i.e., adolescent and parent/legal guardian) and ask them if they are interested in seeing if they qualify to participate in a study about youth well-being and family relationships. If the family is interested in learning more and determining if they qualify for the study, they will be moved to a private area. The assessor will then screen the parent and youth. To protect participants’ sexual minority status, our screening measure also includes questions on levels of physical activity, family communication, quality diet, and substance use. Further, we do not explicitly state that our study has an HSMY focus because qualifying for the study would then identify the status of someone who may not want their sexual minority status revealed. The screening measure is administered via iPads and after the potential participant completes it, the participant will receive a message stating, “you are eligible for this study” or “you are not eligible for this study” based on scores calculated by REDCap, a secure HIPAA compliant software for data collection [18]. If eligible, participants will be informed about the study, including that they will be randomized to potentially participate in adolescent group and family sessions. In our past work with HSMY, many of our participants were referred to the study via word of mouth. In the case where a participant calls or indicates interest in the study, a recruiter will coordinate a time to meet the participant to screen, consent, and assent. Once parent and youth are consented/assented following the screening, they will complete a short assessment battery on a tablet. Following the assessment battery, the youth will be asked to provide a sample of their urine and hair for drug and cortisol testing which will be processed by a qualified lab. The family will then be randomized to one of the two study conditions and compensated for their time. Families are assessed at baseline, 6-, 18-, and 30-months post-baseline. Parents are compensated $55, $60, $65, and $70 cash, for each respective assessment; youths receive $20, $25, $30, and $35 cash, for each respective assessment. To promote participant retention and complete follow-up we will collect participant address, email and telephone where participants can be contacted for follow-up. Participants will also complete a detailed tracking form that includes three secondary contacts (e.g., family, friends) if we are unable to make contact for follow-up assessments.

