#### Main effects

All analyses will be conducted in M*plus* which utilized Full Information Maximum Likelihood to handle missing data [36, 37]. To examine the efficacy of Familias con Orgullo, compared to community practice, in decreasing past 90-day drug use (frequency and quantity) and depressive symptoms among HSMY, over 30-months, we will use latent growth modeling (LGM) [38]. Growth models can be expressed in terms that are identical to multilevel models, where the first level fits each response in time to an individual-level growth model and the second level represents how the slope of outcomes (drug use and depressive symptoms) varies by condition. The second level represents the condition effect on the slope of outcomes (drug use and depressive symptoms). As recommended by Raudenbush and Bryk, we will use 2-level analysis to determine whether the mean trajectories of outcomes for Familias con Orgullo and control differ significantly over time [39]. To account for the non-independence of outcomes, we will conduct multivariate growth modeling similar to that used in evaluating a previous trial [40]. If correlations have above moderate effects (.30 < *r*) [41], we will empirically examine the distinct contributions of the intervention on each separate outcome, using false discovery rate to account for multiple comparisons. Data analysis for this hypothesis and all others will be conducted using M*plus* (v 8.8) [42].

M*plus* Monte Carlo simulation with 10000 replications [43] was used to calculate the power for the main effects outcomes using a latent growth curve model framework with one covariate (i.e., condition assignment) and missing data. With 4 time points and assuming equal sample sizes across both conditions (i.e., 153 cases in each condition) and 20% attrition rate, which is consistent with the attrition in our past studies [12], we have 80% power (assuming a Type I error = .05) to detect a regression coefficient equal to 0.12 (d = 0.36) in the regression of the slope growth factor (for both drug use and depression) on intervention condition. This is considered a small effect size [41, 43].

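### Families enrolled after about June 2025 cannot reach their 30-month assessment before follow-up closes in December 2027

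*Protocol article*

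**What the plan says.** The Materials and methods section fixes the calendar in one sentence: "Recruitment is scheduled to last 21 months from January 2024 and follow-up assessments will run through December 2027". The Study design section sets "four assessments at baseline and 6-, 18-, and 30-months post baseline as the within subject factor", and Recruitment procedures repeats the schedule: "Families are assessed at baseline, 6-, 18-, and 30-months post-baseline". Baseline is each family's own entry point. The assessment battery and samples come first, and then "The family will then be randomized to one of the two study conditions and compensated for their time".

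The Main effects section carries the hypothesis to the same horizon: "decreasing past 90-day drug use (frequency and quantity) and depressive symptoms among HSMY, over 30-months". Its power statement begins "With 4 time points and assuming equal sample sizes across both conditions", takes 153 per arm with 20% attrition, and reports 80% power for a slope coefficient of 0.12 (d = 0.36).

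**The concern.** The recruitment period, the length of follow-up and the closing date cannot all hold for all 306 families. The text mentions no shorter follow-up for late enrollees, no administrative cut-off and no visit window that would absorb the difference.

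This matters because the treatment effect is a difference in slopes over 30 months. With visits at 0, 6, 18 and 30 months, the last wave has the most leverage on the slope, and it is the wave that the calendar removes for late enrollees. The main-effects power statement allows for 20% attrition and says nothing of visits that the closing date rules out.

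**Working it through.** **Inputs from the protocol article.** Recruitment starts in January 2024 and lasts 21 months; assessments end in December 2027 (Materials and methods). The last visit is at 30 months post-baseline (Study design; Recruitment procedures). N = 306, 153 per arm, 20% attrition, d = 0.36, alpha 0.05, 80% power (Main effects).

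**Assumptions not in the article.** Even accrual; a two-sided test; the variances used in step 5.

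**1. Calendar.**
- Months needed: 21 + 30 = 51. Months available, January 2024 to December 2027: 48. Shortfall: 3 months.
- Month 21 of recruitment is September 2025; 30 months later is March 2028. If recruitment starts at the end of January 2024, the last visit moves to April 2028.
- December 2027 minus 30 months is June 2025, which is month 18. The stated dates would agree with an 18-month recruitment period.

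**2. Families affected, even accrual.**
- Months 19 to 21: 3/21 = 14.3%, and 306 × 3/21 = 43.7, about 44 families.
- With a late-January start, 4 of 21 months are affected: 306 × 4/21 = 58.3, about 58 families (19.0%).
- Front-loaded accrual lowers these counts and back-loaded accrual raises them.

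**3. Observed at 30 months (three months affected).**
- As planned: 306 × 0.80 = 244.8.
- With the closing date applied: 306 × (18/21) × 0.80 = 209.8. The observed share is 0.857 × 0.80 = 0.686, so 31% are missing instead of 20%.

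**4. The stated power, as a check.** A simple two-group comparison with 153 × 0.80 = 122.4 per arm and d = 0.36, two-sided 0.05, gives 80.4%. The required n is 122 per arm, and 122/0.80 = 152.5, rounded up to 153. The stated figure reproduces on its own assumptions. If late enrollees were lost altogether, 104.9 per arm would remain and power would be 74.1%. That is a pessimistic bound, because they are not lost altogether.

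**5. Illustrative growth model.** Times are 0, 0.5, 1.5 and 2.5 years, intercept variance 0.5 and residual variance 0.5, with a range of slope variances. For a family seen through wave k with design matrix Z_k, the covariance is V_k = Z_k D Z_k' + 0.5 I, where D is diagonal with the intercept and slope variances. The information is the sum over k of p_k Z_k' V_k⁻¹ Z_k, where p_k is the share of families last seen at wave k. The ratio compares the standard error of the condition effect on the slope with and without the extra 1/7 loss at wave 4. Power is then Φ(2.802/ratio − 1.960), where 2.802 = 1.960 + 0.842.

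The 20% attrition was placed in three ways (in proportion to time, equally across the three follow-up visits, or all before month 6), with and without a condition effect on the intercept:

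| Slope variance | SE ratio | Power in place of 80% |
|---|---|---|
| 0.01 | 1.048–1.051 | 76% |
| 0.05 | 1.043–1.046 | 76–77% |
| 0.10 | 1.038–1.042 | 77% |
| 0.20 | 1.030–1.035 | 77–78% |
| 0.40 | 1.021–1.026 | 78% |

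**The case against.** The strongest reply is that little is lost. Families enrolled in months 1 to 18, about 86% under even accrual, reach 30 months in time. Late enrollees keep three of four waves, and full information maximum likelihood uses them. Loss caused by a closing date applies to both arms alike and is plausibly unrelated to outcome. All of this stands.

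The reply also bears on two stronger readings that a reader might infer. One is that the trial as a whole cannot deliver its 30-month endpoint. The dates do not support that, since only the last three months or so of recruitment are affected. The other is that the treatment effect will be biased or that the sample size is wrong. Nothing in the article shows bias, and the stated power reproduces on its own inputs.

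The power criticism is also confined to the main effects. The mediation and moderation statements assume 20% attrition at each assessment time point. If that is cumulative, it allows 1 − 0.8³ = 49% missing at 30 months, more than the 31% derived here. The wording is ambiguous, and it does not extend to the main-effects statement.

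Finally, Fig 1 is not shown and the article condenses a longer protocol, so one of the dates may be a simple misstatement. In that case no visit is lost and power is unchanged, but the printed dates still need correcting. An early visit window could rescue some visits, but none is stated, and it would have to reach about three months to cover the last families.

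**Conclusion.** The inconsistency is real and should be fixed. The printed calendar is about 3 months short (4 with a late-January start), and families enrolled after about June 2025 have no 30-month visit inside it. The gap itself rests only on the article's dates.

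The size of the consequence rests on assumptions. The figure of about 44 of 306 families (14%) assumes even accrual. The fall from 80% to about 76 to 78% power also depends on variances that the article does not give. On that evidence the harm is a modest loss of precision in the main slope comparison.

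**What to change.** Reconcile the sentence in Materials and methods with the visit schedule in Study design and Recruitment procedures, by one of these routes:

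- **Extend assessments** to about March 2028, or April 2028 if recruitment starts late in January or a visit window is allowed. The cost is three to four more months of assessment visits.
- **Close enrolment by the end of June 2025.** The cost is a faster accrual target: 306/18 = 17.0 families per month instead of 306/21 = 14.6.
- **If neither is possible,** state that 30-month visits falling due after December 2027 are administratively censored, give the expected number, and re-run the main-effects Monte Carlo simulation with that missingness at wave 4 added to the 20% attrition. The cost is one simulation run and a restated power figure.

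If one of the dates is only a misprint, correcting it is enough. The article reports that recruitment had not begun when it was prepared, so at that stage any of these changes was inexpensive.

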**Fig 1 pone.0295683.g001:**
[figure not shown]
Schedule of enrollment, intervention, and assessments.

### Study design

This study uses a randomized trial design with two arms (Familias con Orgullo and community practice) as the between subjects factor with four assessments at baseline and 6-, 18-, and 30-months post baseline as the within subject factor. Dyads of Hispanic youth (*N* = 306) and their primary caregivers (i.e., parents, which may include: mother, father, or legal guardian) will be randomly assigned to Familias con Orgullo or the community practice condition. Participants will be randomized on a 1:1 randomization ratio. An urn randomization will ensure comparability across conditions on the following variables (see measures section below): (1) current drug use (yes/no) and (2) level of depressive symptoms (below 16 on the CES-D or greater than or equal to 16).

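### Randomisation is balanced on baseline drug use and CES-D level, but the main-effects growth model as described names only condition and does not carry these factors; adding them is a free, modest gain

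*Protocol article*

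**What the plan says.** Under Study design, allocation is 1:1 with an urn scheme: "An urn randomization will ensure comparability across conditions on the following variables". The variables are "1) current drug use (yes/no) and (2) level of depressive symptoms (below 16 on the CES-D or greater than or equal to 16". The outcomes have "four assessments at baseline and 6-, 18-, and 30-months post baseline as the within subject factor", so baseline is itself one of the modelled waves.

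Under Main effects, drug use and depressive symptoms are analysed by latent growth modelling, described level by level. For the upper level the article says "The second level represents the condition effect on the slope of outcomes (drug use and depressive symptoms". No other predictor is named there. The power simulation in the same section was run "using a latent growth curve model framework with one covariate (i.e., condition assignment) and missing data", with "i.e., 153 cases in each condition) and 20% attrition rate", and concludes "we have 80% power (assuming a Type I error = .05) to detect a regression coefficient equal to 0.12 (d = 0.36").

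The moderation analysis does list further predictors of the slope (gender, the baseline moderators and their interactions with condition). Neither urn factor is among them.

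**The concern.** Balanced allocation removes chance differences between the arms in the balancing factors, so the treatment contrast varies less from sample to sample than under simple randomisation. A model that leaves the factors out does not know this. Their variance stays in the error term and the reported standard error comes out at or above the true one. The test is then slightly conservative.

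Both factors are likely to predict change: high CES-D scorers tend to regress downward, and youth who do not use drugs at baseline can only stay or go up. At stake is some attainable power on both primary outcomes. Bias and false-positive inflation are not in question.

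**Working it through.** **Inputs from the article.** 153 per arm, 20% attrition, d = 0.36, alpha 0.05. Sidedness is not stated; two-sided is assumed. The article gives no outcome correlation, slope variance, prevalence of use, or share of slope variance explained by the urn factors, so those are assumed below.

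**Step 1: reproduce the stated power.** Retained per arm: 153 × 0.8 = 122.4.

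- z = 0.36 / √(2/122.4) = 2.816
- Power = Φ(2.816 − 1.96) = Φ(0.856) = 80.4%

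The stated 80% reproduces with condition as the only covariate, taking the 20% as one overall loss.

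**Step 2: what adjustment adds when the intercept is free to differ by arm.** Let R² be the share of variance in the individual slopes that the two factors explain, and r = √(1 − R²). With balanced allocation the true standard deviation of the contrast is about r times the unadjusted model standard error, whether or not the analysis adjusts. Therefore:

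- Unadjusted power = Φ(0.856/r)
- Adjusted power = Φ(2.816/r − 1.96)
- Unadjusted Type I error = 2[1 − Φ(1.96/r)]

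| R² (assumed) | r | Unadjusted | Adjusted | Gain (points) |
|---|---|---|---|---|
| 0 | 1.000 | 80.4% | 80.4% | 0 |
| 0.05 | 0.975 | 81.0% | 82.4% | 1.4 |
| 0.10 | 0.949 | 81.7% | 84.3% | 2.7 |
| 0.15 | 0.922 | 82.3% | 86.3% | 4.0 |
| 0.20 | 0.894 | 83.1% | 88.3% | 5.2 |

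At r = 0.95 the unadjusted Type I error is 0.039. Setting the adjusted column against 80.4% would overstate the gain, because the unadjusted test already benefits a little from the balanced allocation.

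**Step 3: check by simulation, intercept free.** Complete data, 122 per arm, visits at 0, 0.5, 1.5 and 2.5 years, allocation balanced within strata (the limit of an urn scheme). Assumed: baseline reliability 0.6 or 0.8, intercept–slope correlation 0 to −0.4, slope SD 0.20 or 0.33. Adding both factors:

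- reduced the model standard error by about 1–8%;
- raised power by about 1–4 points;
- moved Type I error from 0.038–0.047 to 0.045–0.055.

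One case shows the mechanism (reliability 0.6, correlation −0.2, slope SD 0.20). The model standard error fell from 0.0494 to 0.0468, while the empirical standard deviation of the estimate was 0.0468 either way. Power rose from 80.3% to 83.1%.

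A second simulation with other assumed variances (n = 244) gave a standard error 5–9% smaller and power 2–5 points higher. The Step 2 formulas agree: r = 0.95 gives 84.2% − 81.6% = 2.6 points, and r = 0.91 gives 87.2% − 82.7% = 4.5 points.

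**Step 4: common intercept.** With condition acting on the slope only, the second simulation gave a gain of about 0–1 point. In a further check with variance components treated as known and normal data, adding an outcome's own stratum left the standard error unchanged in four scenarios (0.0475, 0.0506, 0.0559 and 0.0471, with and without). That check did not cover a skewed drug-use measure or the other outcome's stratum.

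No scenario showed a loss from adding the factors.

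**The case against.** **The single covariate belongs to the power simulation.** A reader might infer from "using a latent growth curve model framework with one covariate (i.e., condition assignment) and missing data" that the efficacy analysis is fixed with condition alone. The text does not say so; the phrase describes the Monte Carlo run. This stands, and the point is limited to what the described model names.

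**The article condenses a fuller plan.** A covariate list may sit in the full protocol or analysis plan, and the article nowhere excludes the urn factors. This stands as a reason not to call it an error. But the article sets out the efficacy model level by level and names baseline predictors where it wants them, in the moderation models. The described model and the described randomisation do not line up, and one sentence would settle it.

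**Condition is only ever placed on the slope.** Read literally, that implies a common intercept, where the gain is near zero. It would be inconsistent to read silence as no covariates and also as condition on the intercept. This stands: the article does not say whether the arms' intercepts may differ, so both cases must be shown.

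**Baseline is already a modelled wave.** Each factor is a coarse version of a baseline outcome, which limits the gain. The answer is partial, because each factor reflects only one outcome, and the plan provides for examining the outcomes separately.

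**The Huber-White standard errors might deal with it.** They do not by themselves remove this conservatism.

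**Conclusion.** The point holds as a modest, cost-free improvement. The described main-effects model omits the factors on which allocation is balanced. The consequence is a standard error that can be slightly too wide and some forgone power: about 2–5 points if condition also predicts the intercept (1–4 under the other set of assumed variances), and about 0–1 point with a common intercept. These figures rest on assumed variances, complete data and close balance within strata. The gain vanishes if the factors do not predict the slope.

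A reader might infer that planned power is lost. The documents do not support that: the 80% was computed without these factors and reproduces. Nor do they support a figure as high as 88%, which needs an R² of about 0.20 that the article does not supply. Neither bias nor an inflated false-positive rate follows from the omission.

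**What to change.** In the Main effects section, state that:

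- the intercept and slope factors of each primary growth model are regressed on both urn variables (baseline drug use yes/no; CES-D below 16 versus 16 or more), in addition to the effect of condition on the slope;
- the condition effect on the slope is read from this adjusted model;
- the unadjusted model is reported as a sensitivity analysis.

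The cost is two covariates in the model input and a few lines of text. Both variables must be known before allocation, so nothing new is collected. Settling this before outcome data are seen also removes a later choice between adjusted and unadjusted results.
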